## Introduction

 Vaccines are powerful public health tools, significantly reducing illnesses and mortality associated with vaccine-preventable diseases.^1 2^ Childhood vaccinations are especially valuable, as timely immunisation contributes to herd immunity,^3^ limiting the spread of infectious diseases within communities.

Despite their known effectiveness,^4^ coverage of several childhood vaccines has declined worldwide,^5^ falling below the WHO’s 95% recommended threshold.^6^ The UK in particular has experienced a steady decline in the uptake of all childhood vaccines since 2013.^7^ In 2023/2024, coverage in England for the first and second doses of the measles, mumps and rubella vaccine (MMR1 at age 2 years and MMR2 at age 5 years) was 88.9% and 83.9%, respectively.^8^ Liverpool figures were even lower during the same period, with just 81% for MMR1 at age 2 and 73.4% for MMR2 at age 5,^9^ placing the city among the worst performing areas nationally. This has resulted in several outbreaks across England,^10 11^ including a recent cluster of measles cases in Liverpool.^12^

Further compounding this issue are the persistent demographic and socioeconomic inequalities in childhood vaccines uptake.^13^,^16^ Children from deprived communities have notably lower vaccination rates than their peers in more affluent areas, with gaps widening over time.^14^ For instance, the absolute inequality in the uptake of MMR2 between the most and least deprived areas in England widened from 5.3% in 2019 to 11.5% in 2023.^14^

Several factors have contributed to these low and unequal uptake rates, with vaccine hesitancy being among the primary drivers (a delay or refusal to vaccinate despite the availability of vaccines^17^). Hesitancy is often associated with mistrust in healthcare systems, limited engagement with trusted local actors, inadequate communication from healthcare professionals, misinformation and disinformation (deliberate and targeted spreading of misinformation).^18 19^ These factors may intersect with structural barriers, such as inflexible appointment systems, further discouraging the uptake.^19^

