### Analysis

We will use the SCM, an observational quasi-experimental approach that extends the traditional difference-in-differences (DiD) framework,^27^ to estimate the impact of the intervention on childhood vaccine uptake. While DiD assumes that the intervention and comparison groups would have followed parallel trends in the absence of the intervention, SCM constructs a weighted combination of untreated units, called a ‘synthetic control’, that mirrors the pre-intervention characteristics and outcome trends (ie, vaccine uptake) of the intervention units.^28^ This allows for a more robust estimation of the counterfactual, particularly when the parallel trends assumption is unlikely to hold. This method has been previously used to evaluate the population-level impact of various public health interventions,^34 35^ including those targeting vaccine uptake,^36 37^ demonstrating its suitability for the current study.

GPs will serve as our unit of analysis, with the target population being registered children aged under 5 years who were eligible for routine childhood vaccinations between April 2019 and March 2025, as reported in the COVER dataset. The intervention group is defined as practices whose population-weighted centroids fell within a 1 km radius of any of the nine intervention sites. As such, 19 practices will be included in the intervention group (see figure 2), with all remaining practices in England forming the donor pool for constructing the synthetic control group. We will apply SCM for microdata,^38^ which is specifically suited to settings involving numerous small scale units, such as GPs. Matching will be performed using calibration weights for the pre-intervention uptake of included vaccines and the previously mentioned covariates. The final inclusion of covariates in the SCM will also be guided by their practical contribution to achieving balance between intervention and control units.

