**Figure 2 F2:**
[figure not shown]
Coverage of MMR1 at 2 years and MMR2 at 5 years across Liverpool by MSOA in the year preceding the intervention (April 2022 to March 2023). Red dots with green circles represent the locations of intervention events with a 1 km surrounding buffer, and cyan dots represent the population-weighted centroid of intervention GPs. Coverage data are based on GP-level uptake reported through the COVER programme. COVER, Cover of Vaccination Evaluated Rapidly; GP, general practice; MMR, measles, mumps and rubella; MSOA, Middle Layer Super Output Area.

The pre-intervention period spans Q1 to Q18 (April 2019 to September 2023), with Q19 to Q24 (October 2023 to March 2025) defining the post-intervention period. The average treatment effect will be estimated as the average difference in vaccine uptake between the intervention and synthetic control groups in the post-intervention period.

The statistical significance of estimated effects will be assessed using the permutation inference, following the method described by Robbins and Davenport.^39^ We will perform 250 permutations, reassigning treatment status to control units to generate a distribution of treatment effects under the null hypothesis (ie, no difference in vaccine uptake between the intervention and control groups). All analyses will be conducted using R V.4.4.2 and the microsynth package.^39^

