### Sensitivity analysis

Given the community-based nature of the intervention, there is potential for spillover effects beyond the identified intervention practices. To mitigate this effect, we will conduct a sensitivity analysis excluding other non-intervention GPs located within the central and north Liverpool PCNs from the donor pool practices used to construct the synthetic control group. We will also incorporate a one-quarter lag at the start of the post-intervention period (ie, starts at Q20 instead of Q19) to allow sufficient time for any changes in vaccine uptake to become observable.

To assess the sensitivity of the estimated effect to the exposure’s spatial definition, we will test alternative buffer distances (0.5 km, 1.5 km and 2 km) from intervention event sites. We will further attempt to exclude practices that may have been affected by other concurrent vaccine-related initiatives implemented elsewhere in England. To identify such initiatives, an audit of interventions form will be distributed to immunisation leads at the UK Health Security Agency and to public health leads across the nine local authorities in Cheshire and Merseyside via the Champs Public Health Collaborative. A copy of the form is provided in online supplemental material 1.

Further sensitivity analyses will involve adjusting the pre-intervention period to begin after the final phase of national COVID-19 restrictions in England (February 2022 to Q12 in our dataset), as it could bias the counterfactual estimation. For example, tiered restrictions during the pandemic varied in stringency across England. This has led to regional variation in childhood vaccine uptake^40^ and will consequently affect the SCM matching.

In addition, we will rerun the evaluation using vaccine uptake aggregated to a small area neighbourhood level (LSOA), which may better reflect the community-based nature of the intervention. Finally, to test the robustness of our findings, we will explore alternative approaches to constructing synthetic controls. These may include methods that incorporate negative control series or rely on different assumptions about the counterfactual.

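### Most of any Liverpool-wide change in MMR uptake after October 2023 would be credited to HELP, and no committed check separates the two

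*Protocol article*

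**What the plan says.** The Analysis section of the protocol article states that "19 practices will be included in the intervention group", defined by closeness to nine event sites in Liverpool, "with all remaining practices in England forming the donor pool for constructing the synthetic control group". On the weights it says: "Matching will be performed using calibration weights for the pre-intervention uptake of included vaccines and the previously mentioned covariates". The covariates described in the text and in Table 2 cover child population, deprivation, ethnicity, practice capacity, patient survey measures and distance. None is a city or region term.

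The effect is the "average difference in vaccine uptake between the intervention and synthetic control groups in the post-intervention period", with "Q19 to Q24 (October 2023 to March 2025) defining the post-intervention period".

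The Sensitivity analysis section lists:
- a spillover run, "excluding other non-intervention GPs located within the central and north Liverpool PCNs from the donor pool";
- a one-quarter lag;
- buffers of 0.5, 1.5 and 2 km;
- exclusion of practices touched by other vaccine initiatives elsewhere in England, informed by an audit form;
- a pre-period that starts after COVID-19 restrictions;
- a rerun at small-area (LSOA) level;
- an exploration of other synthetic control methods, worded as optional and with no method fixed.

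The Introduction describes several outbreaks across England, "including a recent cluster of measles cases in Liverpool". It gives no date for the cluster.

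**The concern.** A synthetic control removes differences that show in the pre-intervention data. It cannot remove an event that starts after the matching window and acts on the treated units but on few of their donors. With every treated practice in one city and donors from the whole country, a post-October-2023 event in that city is such an event. The primary outcomes are MMR doses, so a local response to measles is an obvious candidate.

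At stake is attribution. The study asks whether HELP raised uptake. If uptake rose across Liverpool for another reason, the plan gives no committed way to tell that rise from a HELP effect. The committed runs could also agree with one another because they share the same national comparison, and that agreement could be read as robustness.

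**Working it through.** **No figure to reproduce.** The protocol states no bias, power or weight figure for this point. The quarter labels are consistent: September 2023 falls in Q18, October 2023 in Q19, March 2025 in Q24.

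**Algebra.** Let d be a uniform Liverpool-wide shift after October 2023, h the true HELP effect and w the total synthetic-control weight on Liverpool donors. The treated mean moves by h + d and the synthetic control by w × d, so

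estimate = h + (1 - w) × d.

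**Size of w by counting.** The protocol gives neither the number of donor practices N nor the number L of those in Liverpool. Assume N of 5,500 or 6,500 and L of 40 to 80. If each Liverpool donor gets m times the weight of another donor, w = mL / (mL + N - L).

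| m | 1 - w at N = 5,500, L = 80 | 1 - w at N = 6,500, L = 40 |
|---|---|---|
| 1 | 1 - 80/5,500 = 98.5% | 1 - 40/6,500 = 99.4% |
| 3 | 1 - 240/5,660 = 95.8% | 1 - 120/6,580 = 98.2% |
| 10 | 1 - 800/6,220 = 87.1% | 1 - 400/6,860 = 94.2% |
| 30 | 1 - 2,400/7,820 = 69.3% | 1 - 1,200/7,660 = 84.3% |

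**Size of w by simulated calibration.** Matching on low uptake and deprivation can pull weight towards Liverpool, so two simulations with no HELP effect were run on different assumptions.

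1. 6,300 donors, 60 of them in Liverpool, 18 pre-period quarters and 9 covariates, 10 replicates per setting. Liverpool donors took about 20% to 30% of the weight on average. A 5-point city-wide rise gave primary estimates of 2.9 to 4.0 points (2.911/5 = 58% to 4.044/5 = 81%). With half of the Liverpool donors removed, as a stand-in for the spillover run, it gave 3.3 to 4.4 points (66% to 88%). With no rise, the estimates lay between -0.5 and 0.1, so the percentages are approximate.
2. 6,000 donors, 19 treated, 20 other practices in the target PCNs, 40 other Liverpool practices, 80 replicates. For MMR1 at 2, MMR1 at 5 and MMR2 at 5, a 2-point rise moved the primary estimate from -0.61, 0.16, 0.17 to 1.19, 1.93, 1.92. That is a change of 1.80, 1.77 and 1.75 points, or 88% to 90% of the rise. The spillover run moved by 1.84, 1.81 and 1.78.

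**Permutation test.** Placebo sets of 19 practices scattered over England do not share a city shock. With no HELP effect, 250 permutations, a 5% level and the whole shock passed through (w = 0), a 2-point shock was declared significant in 83%, 38% and 18% of runs for assumed practice-level SDs of 3, 5 and 8 points. With a 1-point shock the figures were 28%, 13% and 7%, and with no shock about 4% to 5%.

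**The committed checks.**
- The spillover run lowers w, so 1 - w rises.
- The lag and post-COVID runs change timing, not the comparator.
- The buffers change who counts as exposed. A city-wide shift would show as an effect that does not fade with distance, which is only indirect evidence.
- The concurrent-initiative exclusion concerns places elsewhere in England, and no rule is given for something else acting on the treated practices.
- For the LSOA rerun no donor pool is stated.

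**A rest-of-Liverpool contrast.** With donors outside Liverpool w = 0, so the gap for the 19 practices is h + d, the gap for unexposed Liverpool practices is d, and the difference is h. In simulation 2, under the 2-point rise, the difference averaged -0.07, 0.02 and 0.04. The SDs rose from 1.14, 0.53 and 0.92 to 1.39, 0.67 and 1.10, ratios of 1.22, 1.26 and 1.20. A rough check with independent gaps and equal practice-level variance agrees: √(1 + 19/40) = 1.21. With half as many comparison practices it would be √(1 + 19/20) = 1.40.

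**The case against.** The strongest reply is that the plan does include Liverpool comparators. Every non-intervention Liverpool practice is in the primary donor pool, and the spillover run removes only those in the central and north PCNs. That is correct. A reader might infer that Liverpool is absent from the comparison, or that a city-wide change passes through almost in full. The documents support neither. What is missing is a contrast that isolates Liverpool, and with w unstated the pass-through can be well below 100%.

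It can also be said that nothing shows a shock took place. This stands. The cluster is undated and is mentioned among outbreaks across England, so matched low-uptake donors may have reacted too. The remark on the pandemic, "This has led to regional variation in childhood vaccine uptake", concerns the pre-intervention period, for which the plan has a rerun. It is not evidence of a regional event after October 2023. Nor can one say that the audit overlooks outbreaks, because the form is in a supplement that is not shown.

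The optional last check could include a suitable method, but no method is committed to. The limitations admit residual confounding and unidentified initiatives, yet name no local event acting on the treated practices.

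Finally, the simulated shift is uniform over the city, so the contrast cancels it by construction. A response confined to central and north Liverpool, where the protocol places the lowest uptake and the greatest deprivation, would not cancel.

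**Conclusion.** The point holds as a limit on what the design can attribute. A Liverpool-wide change in MMR uptake after October 2023 would be credited mostly to HELP: about 60% to 99% of it, depending on the weight that falls on Liverpool donors. No committed analysis would separate it from a HELP effect, and the spillover run makes this bias slightly larger. The range rests on assumed practice counts, weight tilts and simulated data. The direction follows from the algebra alone, provided w is below 1. It is not a finding that the estimate will be biased, since the protocol does not show that a city-wide change happened. The addition is cheap and worth making, and the primary analysis need not change.

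**What to change.** Add one pre-specified sensitivity analysis. With all donors taken from outside Liverpool, fit the same synthetic control to (a) the 19 practices and (b) Liverpool practices that lie outside the central and north PCNs and more than 2 km from any event site. Report (a), (b) and (a) minus (b) beside the primary estimate, with no rule that lets the contrast replace the primary. A rule to credit HELP only with the excess once (b) looks non-zero would be an undefined pretest and could subtract real benefit. If (b) is similar to (a), state that a HELP effect cannot be separated from a city-wide change.

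The cost is one further run on data the study already uses, and it can be fixed now because analysis starts only after the audit planned for January to April 2026. The contrast is less precise than the primary estimate (SD about 20% to 26% larger with 40 comparison practices, more with fewer). It is conservative if HELP's digital material reached the whole city, and it does not remove a shock confined to central and north Liverpool. These limits should be stated with the result.

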**Figure 2 F2:**
[figure not shown]
Coverage of MMR1 at 2 years and MMR2 at 5 years across Liverpool by MSOA in the year preceding the intervention (April 2022 to March 2023). Red dots with green circles represent the locations of intervention events with a 1 km surrounding buffer, and cyan dots represent the population-weighted centroid of intervention GPs. Coverage data are based on GP-level uptake reported through the COVER programme. COVER, Cover of Vaccination Evaluated Rapidly; GP, general practice; MMR, measles, mumps and rubella; MSOA, Middle Layer Super Output Area.

The pre-intervention period spans Q1 to Q18 (April 2019 to September 2023), with Q19 to Q24 (October 2023 to March 2025) defining the post-intervention period. The average treatment effect will be estimated as the average difference in vaccine uptake between the intervention and synthetic control groups in the post-intervention period.

The statistical significance of estimated effects will be assessed using the permutation inference, following the method described by Robbins and Davenport.^39^ We will perform 250 permutations, reassigning treatment status to control units to generate a distribution of treatment effects under the null hypothesis (ie, no difference in vaccine uptake between the intervention and control groups). All analyses will be conducted using R V.4.4.2 and the microsynth package.^39^

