## Methods and analysis

### Data sources and measures

#### Vaccine uptake

This study will use publicly available data from the Cover of Vaccination Evaluated Rapidly (COVER) programme,^29^ which provides quarterly statistics on the uptake of routine childhood immunisations for children aged 5 years and under at the general practice (GP) level in England.

Our primary outcome is the uptake of the first and second doses of MMR vaccine (MMR1 and MMR2). We will further examine the 6-in-1 vaccine, PCV booster dose and rotavirus vaccine as secondary outcomes, as they are administered at similar ages and often coincide with MMR. Table 1 provides information on the age at which each vaccine is administered, based on the UK childhood vaccination schedule,^30^ and its corresponding COVER reporting age.

**Table 1 T1:** Childhood vaccines included in the analysis, with their recommended administration ages and corresponding measurement points in the COVER dataset

Vaccine	Age administered	Age measured in COVER
DTaP/IPV/Hib/ HepB (6-in-1)	8, 12, 16 weeks	12 months
Rotavirus	8, 12 weeks	12 months
PCV booster	13 months	2 years
MMR1	13 months	2 years, 5 years
MMR2	3 years 4 months	5 years

COVER, Cover of Vaccination Evaluated Rapidly; DTaP, diphtheria, tetanus, pertussis; HepB, hepatitis B; Hib, haemophilus influenzae type B; IPV, inactivated polio vaccine; MenC, meningococcal group C; MMR, measles, mumps and rubella; PCV, pneumococcal conjugate vaccine.

COVER reports vaccine uptake as the percentage of eligible children who received the vaccine by a certain age within a given quarter. A key strength of this dataset is its completeness, with a near universal coverage across the GP-registered child population in England. We will use data spanning 24 consecutive quarters, from April 2019 (the earliest quarter with GP-level data) to March 2025, labelled sequentially from Quarter 1 (Q1) to Quarter 24 (Q24).

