Average distance from GP	A proxy measure of geographical accessibility. This variable represents the average straight-line distance between the GP practice and its registered population, calculated using the LSOA centroid of each patient’s area. For each GP, distances from the centroid of each LSOA where patients are registered will be calculated to the GP’s location. A weighted average will then be derived, with weights based on the number of registered children per LSOA.	NHS England Digital (for GP registered population by LSOA) ONS Open Geography Portal (LSOA centroids) ONS Open Geography Portal (GP physical location)	Single time point at the intervention starting point (October 2023)

* National general practice profiles, available via the department of health and social care fingertips platform.

GP, General practice; IMD, English Index of Multiple Deprivation; LSOA, Lower layer Super Output Area (a statistical geographical unit in the UK that represent a small area usually compromising of 1500 residents); NHS, National Health Service; ONS, Office for National Statistics; PCN, primary care network; QOF, Quality and Outcomes Framework.

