### Intervention details

The intervention targeted parents and carers of children aged 13 months to 5 years and 11 months who were registered with practices in the central and north Liverpool primary care networks (PCNs), areas known for lower childhood vaccination rates and higher levels of deprivation.

Activities were designed and delivered as part of a community-led, creative health approach. The model adapted standard quality improvement (QI) tools for use in community settings and was implemented through establishing a multidisciplinary Community Innovation Team (CIT) comprising community organisations, volunteers, community champions, creatives, primary care and public health professionals. The team received phased training in QI methodology, beginning with the use of local GP data to identify and target populations with low uptake.

To inform intervention design, the CIT conducted a behavioural insight survey with 116 parents and carers of partially or unvaccinated children aged 1–5 years and consulted local health providers involved in childhood vaccination. This was followed by a structured root cause analysis to identify feasible priority actions that tackle root causes locally. Findings revealed widespread concerns about vaccine safety and efficacy, difficulty in identifying misinformation and reduced trust in health authorities and National Health Service (NHS) information. In response, the CIT co-developed a multicomponent intervention to deliver locally relevant health messaging.

The intervention was implemented between 1 September 2023 and 1 June 2024 across central and northern Liverpool. Activities included community outreach events, school-based coffee mornings and a series of reflective discussions, all of which were designed to increase awareness of the MMR vaccine, build trust and support parents and carers in accessing vaccination services. In total, 22 events were held across nine sites. These were supplemented by digital and printed education material, including targeted MMR-related YouTube video links, ‘Measles Machine’ flyers and reminder text messages sent to nearly 2000 parents of partially or unvaccinated children.

Informed by the behavioural insights survey findings, we developed a conceptual diagram representing an a priori hypothesis of how the HELP intervention is expected to influence childhood vaccine uptake (figure 1).

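### The last of the 18 matching quarters (Q18, July to September 2023) is partly exposed to HELP, and no planned analysis takes it out of matching

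*Protocol article*

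**What the plan says.** All places are in the protocol article.

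- **Launch.** Intervention details: "The intervention was implemented between 1 September 2023 and 1 June 2024". The Abstract also gives September 2023 to June 2024.
- **Quarters.** Vaccine uptake: 24 quarters from April 2019 to March 2025, "labelled sequentially from Quarter 1 (Q1) to Quarter 24 (Q24").
- **Windows.** Analysis: "The pre-intervention period spans Q1 to Q18 (April 2019 to September 2023"), "with Q19 to Q24 (October 2023 to March 2025) defining the post-intervention period".
- **Matching.** Analysis: "Matching will be performed using calibration weights for the pre-intervention uptake of included vaccines and the previously mentioned covariates". No quarter of the pre-period is excepted.
- **A second start date.** Table 2, in the row on average distance from the practice: "Single time point at the intervention starting point (October 2023").
- **Lag analysis.** Sensitivity analysis: a "one-quarter lag at the start of the post-intervention period (ie, starts at Q20 instead of Q19"). The end of the pre-period is not mentioned.

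**The concern.** A synthetic control stands for what would have happened without the programme, so the quarters used to build it should be free of the programme. By the article's own dates, the last matching quarter is not. If uptake in the 19 intervention practices began to rise in September 2023, the weights are asked to reproduce part of that rise, and the same amount is missing from the later contrast. For a positive effect the error goes one way, toward no effect.

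Some components could act quickly. Intervention details mentions reminder texts to nearly 2000 parents of partially vaccinated or unvaccinated children. Neither the texts nor the 22 events are dated, so a September response cannot be ruled out.

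None of the planned analyses would reveal the problem. The lag analysis moves only the start of the effect window. The COVID-19 analysis moves only the start of the pre-period. The buffer, donor-pool and small-area analyses leave the time windows alone, and the alternative synthetic control methods do not commit to dropping Q18.

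**Working it through.** **Inputs.** Programme dates: 1 September 2023 to 1 June 2024 (Intervention details). Quarters: consecutive three-month periods from April 2019 (Vaccine uptake). Outcome: children vaccinated by a reporting age of 12 months, 2 years or 5 years (Vaccine uptake, Table 1). Target group: carers of children aged 13 months to 5 years 11 months (Intervention details). Anticipated effect: 5 to 15 percentage points (Expected results).

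**Step 1: the plan's own labels.** Q1 is April to June 2019. Counting forward, Q17 is April to June 2023, Q18 is 1 July to 30 September 2023, and Q19 starts on 1 October 2023. The stated spans reproduce.

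**Step 2: programme days in each quarter.**

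| Quarter | Days in quarter | Programme days | Share |
|---|---|---|---|
| Q17 | 91 | 0 | 0% |
| Q18 | 92 | 30 | 32.6% |
| Q19 | 92 | 92 | 100% |
| Q20 | 91 | 91 | 100% |
| Q21 | 91 | 62 | 68.1% |
| Q22 to Q24 | – | 0 | 0% |

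The total is 30 + 92 + 91 + 62 = 275 days. September is 30/275 = 10.9% of the programme. If the 22 events were evenly spread (an assumption), about 22 × 0.109 = 2.4 of them fell in September.

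**Step 3: which Q18 outcomes can be affected.** COVER counts doses received by the reporting age. A child who reached that age in July or August was counted before launch. With birthdays evenly spread (an assumption), at most 30/92 = 32.6% of the Q18 cohort could be exposed, by about 15 days on average. 6-in-1 and rotavirus are measured at 12 months, below the target age. The outcomes at issue are therefore the PCV booster and MMR1 at 2 years, and MMR1 and MMR2 at 5 years.

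**Step 4: shift in the Q18 value.**

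- *Extreme ceiling: full effect at once in every child reaching the reporting age in September.* Shift = effect × 30/92. For 5 points: 5 × 0.326 = 1.6. For 15 points: 15 × 0.326 = 4.9.
- *Linear build-up over 275 days (an assumption).* A child reaching the age on day k has k/275 of the effect. Averaged over the quarter: (1 + 2 + … + 30)/(275 × 92) = 465/25,300 = 0.0184. For 5 points: 0.09. For 15 points: 0.28.

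**Step 5: shift in the counterfactual.** This depends on how far a shift in Q18 carries into the weights, which the article does not fix. Three illustrations, each using the Step 4 ceiling:

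- Q18 as one of 18 equally weighted quarters: 1.63/18 = 0.09 to 4.89/18 = 0.27 points.
- COVID-19 analysis, equal weights: 1.63/7 = 0.23 to 4.89/7 = 0.70 points if the period starts at Q12 (seven quarters), or 1.63/6 = 0.27 to 4.89/6 = 0.82 points if it starts at Q13 (six). The wording allows either start.
- The whole ceiling carried forward: 1.6 to 4.9 points.

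**Step 6: after the change.** Matching on Q1 to Q17 leaves 17 quarters with no programme days. The effect window stays at the six quarters Q19 to Q24.

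**The case against.** With quarterly data, a launch in the last third of a quarter has to be assigned somewhere. Q18 is two thirds unexposed, keeping it preserves the most recent baseline, and any bias from a real benefit is conservative. Matching also draws on 17 clean quarters and a broad set of covariates. The October 2023 entry in Table 2 dates a single distance covariate and does not alter outcome matching.

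Most of this stands, and it limits the point to a small one. It does not remove it: the article gives no reason for the assignment, and no planned analysis tests it.

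Three stronger readings are tempting, and the article does not support them.

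- *The synthetic control is generally calibrated to exposed uptake.* It is not. Seventeen of 18 matching quarters have no programme days, and about two thirds of the Q18 cohort had passed the reporting age before launch.
- *No clean check of pre-launch fit is left.* Q17 and all earlier quarters are unexposed, and fit can be inspected there.
- *The lag analysis matches on Q19, which is wholly inside the programme.* The text moves only the start of the effect window. The natural reading is that Q19 is simply dropped. A clause to say so is worth adding, but the text shows no error here.

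**Conclusion.** The point holds in a limited form. By the article's own dates, the last matching quarter is exposed for 30 of 92 days, and the start date is inconsistent between Intervention details, Table 2 and the Analysis section. For a positive effect, the MMR and PCV booster estimates can be pulled slightly toward zero. The 12-month outcomes lie outside the target age in that quarter.

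The likely shift in the Q18 value is about 0.1 to 0.3 points, with an extreme ceiling of 1.6 to 4.9. These figures rest on the anticipated 5 to 15 points, evenly spread birthdays and, for the lower range, a linear build-up. The article does not date the single events or the text messages, so the assumptions cannot be checked. The calendar overlap is certain if 1 September 2023 is the true start. If reconciling the dates showed that nothing took place before October, Q18 would be clean.

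The change is worth making because it costs little and analysis has not begun: the Timeline places it after the audit planned for January to April 2026.

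**What to change.** 1. End the matching period at Q17 (June 2023). Treat Q18 as a transition quarter, left out of both matching and effect estimation, and keep the effect window at Q19 to Q24. At minimum, add a sensitivity analysis that does this.
2. Add a clause to the lag analysis saying that Q19 is left out of the effect window and is not used for matching.
3. Reconcile the start date across Intervention details (1 September 2023), Table 2 (October 2023) and the Analysis section (pre-period to the end of September 2023). If the October entry is only the snapshot date of the distance covariate, label it so.

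Cost: one index in the code, a few words, and one of 18 matching quarters. In the COVID-19 analysis it leaves six matching quarters (Q12 to Q17) or five (Q13 to Q17). No new data are needed.
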